### Study timelines

All patients seeking emergency consultation at the dental subunits of the Nantes University Hospital will be screened for the selection criteria. If a patient meets all criteria, he or she will be informed by an investigator and the investigation team of study technicians. He or she will be handed an information letter that comprises the objectives, methods, follow-up risks and restrictions of the trial. The patient’s oral consent is required before the start of any intervention and will be under the responsibility of the investigator to obtain consent. Thus, the patient’s consent will be obtained by the investigators only (Fig. 1).

**Fig. 1 Fig1:**
[figure not shown]
Flowchart of a trial evaluating the noninferiority of ICA QuickSleeper™ system versus IANB anaesthesia for the pain management in the emergency care of irreversible pulpitis in mandibular molars at the Nantes University Hospital

The investigator in charge of the emergency room will proceed to randomisation (see below) using a secure computer program called Ennov Clinical and will conduct the emergency endodontic treatment. The patient will then be contacted by a research assistant 72h following the intervention by telephone to assess the pain perception and if any secondary effects of the anaesthesia occurred, as depicted in Table 1. Part or all of the study may be discontinued permanently or temporarily by the decision of the ANSM, the CPP, and the Study Sponsor (Nantes University Hospital).

**Table 1 Tab1:**
[figure not shown]
Schedule of enrolment, interventions, and assessments during COQ study protocol

### Auditing

The audit process will be done independently from investigators and the sponsor.

### Interventions

The patient will be blinded to the affected group and will fill out the first questionnaire which is the French version of Corah’s dental anxiety scale [31] to assess his or her anxiety about dental care. Then, the patient will be placed with a cuff on the arm, and a pulse oximeter on the other finger connected to a blood pressure monitor to monitor the cardiovascular parameters (heart rate, systolic and diastolic blood pressure, and oxygen saturation) throughout the intervention.

### Sequence generation

Each patient, regardless of the study group allocated, will receive 1.8 mL of 4% articaine 1:100 000 for 2 min. The evaluated intervention consists of the administration of intraosseous anaesthesia using the QuickSleeper™ (DHT, Cholet, France) system, according to the manufacturer’s recommendations, in the “ICA” group. A plastic syringe with a cartridge of 4% articaine 1:100,000 epinephrine will be used in the “IANB” group. The emergency treatment will be a pulpotomy. The tooth will be isolated with a rubber dam and all carious tissue and pulpal parenchyma will be removed. Pulpal bleeding will be controlled using a 2.5% sodium hypochlorite and the site will be covered with calcium hydroxide and a temporary filling. At the end of the intervention, all patients, regardless of the randomisation group, will be given two types of antalgics (paracetamol 1 g or paracetamol 600mg/codeine 50 mg) according to preoperative pain declaration (VAS) and recommended to take them only if they experience pain, according to the good clinical recommendations.

### Randomisation

Patients will be randomly assigned to one of the two arms: “ICA” and “IANB” at a ratio of 1:1. The randomisation list will be computer-generated by the study statistician and the randomisation process will be centralised through a secured clinical data processing website managed by Ennov© Clinical system software (Ennov, Paris, France). The investigators will enter the patient’s information (initials, age, and date of birth mentioning the month and year only), and the software will provide the patient’s unique allocation number and randomisation group.

### Allocation concealment mechanism

As it is a randomised controlled study, the patients are blinded. The unblinding occurs if a patient decides to leave the protocol prematurely. The best care will be provided by the investigator and the pulpotomy will be performed under the best conditions to relieve the patient’s pain.

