Obtaining anaesthesia in patients with endodontic pain of pulpal origin is often difficult to achieve despite supplemental buccal infiltrations in addition to nerve blocks [7]. The failure rate is between 44 and 81% as was described in various clinical studies [8–10]. In addition, mandibular molars are the most difficult to anaesthetise [11]. In mandibular molars, there is an IANB failure rate of 15% up to 58% for non-inflammatory pulpitis [12, 13] and 44 to 81% for irreversible pulpitis [14–17]. IANB is performed blindly and guided only by anatomic landmarks that vary from individual to individual. Furthermore, there is a variation in the physicochemical characteristics such as lowered pH in the inflamed tissue that neutralises the base form of the anaesthetic in the nerve sheath and membrane. Furthermore, there are altered resting potentials and lowered thresholds of the excitability of the nerves in the inflamed tissue that leads to a varied state of innervation [18]. In addition, psychological factors (fear, anxiety) from one individual to another leads to a state of hyperalgesia or no analgesia that adds to the difficulties in achieving successful pulpal anaesthesia.

Anaesthetics called intra-osseous (IO) could be a more effective alternative. IO consists of depositing the anaesthetic solution into the alveolar bone supporting the teeth. In this method, anaesthesia begins immediately after the injection without causing soft tissue numbness. The injection scarcely causes any pain, and it requires relatively fewer amounts of the anaesthetic solution compared to conventional nerve block techniques [19, 20]. Several types of intraosseous anaesthetic system have been commercialised and studied clinically, such as the Wand® (Milestone Scientific, USA), the X-Tip (Dentsply, York, PA) and Stabident™ (Fairfax Dental Inc., Miami, FL) systems.

Several forms exist: intra-septal (IS), intra-diploid (ID), and more recently, intra-osseous computerised anaesthesia (ICA). However, IS administers the anaesthetic solution into the bone septum just after the cortex, a dense and reduced area, that may lead to partial or complete necrosis [21].

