Intra-osseous computerised anaesthesia (ICA), such as the QuickSleeper™ system (Dental Hi-Tec, Cholet, France), administers the solution with a computerised control into the diploë (a richly vascularized bone) at a local rate and pressure. Thus, the QuickSleeper™ system is a form of ID in which the anaesthetic is delivered close to the root apices and associated periradicular tissues, leading to a greater reduction in periradicular sensation. The anaesthesia takes effect more rapidly since the solution is deposited close to the apex of the tooth at an axis of 15° to 30°. Thus, this form of delivery increases its effectiveness and reduces the risk of tissue necrosis, with better pain control (42 to 93% according to studies) [22, 23]. No soft tissue numbness occurs, and relatively fewer amounts of anaesthetic solution are needed. However, due to the fast diffusion of the anaesthetic solution in the diploe, the heart rate accelerates via the added effect of vasoconstrictors. This elevation is transient, and its effect is negligible and does not pose serious cardiovascular risk [12, 22].

There are currently many clinical studies that have evaluated cardiac parameters during IO administration. The heart rate increases in a reversible manner depending on the speed of injection [12]. The Stabident™ system showed a significant increase in heart rate of 8-28 beats/minute (BPM) on average with 2% lidocaine 1:100,000 epinephrine according to 3 authors [24–26]. By comparison, the X-Tip injection elevated the heart rate by 9–10 beats per min [27]. In regard to other parameters such as oxygen saturation and blood pressure, Pereira et al found no differences in either of them when using the X-Tip™ system but noted a significant increase in heart rate with 4% articaine (1:100,000 or 1:200,000 epinephrine) for anaesthetizing irreversible pulpitis lower molars [23]. Therefore, the accelerated heart rate could be a potential adverse effect of this injection [27].

Articaine is a common anaesthetic agent and a member of the amide family. The presence of its thiophene group increases its liposolubility, facilitating its diffusion into both nerve sheaths (such as the inferior alveolar nerve) and neural membranes of individual axons comprising a nerve trunk. The lower pKa of articaine would translate into a greater percentage of the drug in the active base form and its plasma protein binding is 95% higher than most other local anaesthetics [25–27].

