### Design

This noninferiority, prospective, randomised, controlled, single-blind, two-group study will be conducted in the emergency subunits of the Nantes University Hospital. Eligible patients with irreversible pulpitis in the first or second mandibular molars requiring emergency dental care will be included in the study. Diagnosis will be based on clinical and radiographic examination. Two parallel groups will be randomised at a ratio of 1:1 so that patients will either receive (1) intraosseous anaesthesia or (2) inferior alveolar nerve block anaesthesia. This manuscript used the SPIRIT reporting guidelines [30].

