## Discussion

Computerised intraosseous anaesthesia has gained considerable interest among practitioners in the last 25 years [32]. Wand® (Milestone Scientific, USA) was the first system used in 1997. What IO systems have in common is that the computer system controls the speed and pressure of the infiltration of the anaesthetic solution, to reduce pain, discomfort, and anxiety of the patient. Therefore, they are better alternatives to conventional bloc anaesthesia to counter IANB failure or as a first intention.

Vincent’s sign is the collateral effect of traditional IANB with ipsilateral lower lip anaesthesia, commonly used by clinicians as evidence of a successful anaesthetic procedure. However, this does not confirm that a successful pulpal anaesthesia has been obtained. Furthermore, accidental biting and burning of the lip and tongue (due to prolonged labial anaesthesia), as well as potential risks of mandibular nerve injury or a localised hematoma of the vascular lesion could occur. This further encumbers the advantages of this technique when comparing it to IO systems.

Very few valid clinical trials exist on the subject, most being realised with systems of intradiploid (ID) anaesthesia other than QuickSleeper™. Several studies have shown that supplemental Stabident™ ID injection, when added to IAN block and using local anaesthetics with vasoconstrictors, significantly increased the success of pulpal anaesthesia for 60 min [33].

One of the most important aspects of any primary anaesthetic technique is the pain experienced during the injection. This is particularly important for patients suffering from pain and stress due to an acute inflammation of the pulp. IANB, in particular, has been considered a fairly painful injection in the acute pulpitis situation. Owing to its asymmetric triple bevel, the needle tip in the QuickSleeper™ system makes possible a painless and easy perforation into the bone. The patient would report no pain or mild pain during perforation and solution deposition, despite the long wait for the agent to deposit. In addition, slow injection of more than a minute results in higher success rates [12, 22, 25]. The study by Özer has concluded that the pain levels after slow administration of QuickSleeper™ resulted in 82.5% success in mandibular third molars in assessing anaesthetic efficacy [29].

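### Patients are declared blinded, but the article's own account of lip numbness makes blinding unlikely to last past the injection, so later patient-reported outcomes cannot be treated as blinded

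*Protocol article*

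**What the plan says.** The Abstract and the Design section both use the single-blind label; the latter reads "This noninferiority, prospective, randomised, controlled, single-blind, two-group study will be conducted in the emergency subunits". Two further sections say who is blinded. Interventions states "The patient will be blinded to the affected group and will fill out the first questionnaire". Allocation concealment mechanism states "As it is a randomised controlled study, the patients are blinded", and adds that unblinding happens when a patient leaves the protocol early.

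The article also describes what each injection does to the soft tissues. On intraosseous injection in general, the Background says "In this method, anaesthesia begins immediately after the injection without causing soft tissue numbness". On the trial's own device it says "No soft tissue numbness occurs, and relatively fewer amounts of anaesthetic solution are needed". On the comparator, the Discussion says "Vincent’s sign is the collateral effect of traditional IANB with ipsilateral lower lip anaesthesia". It notes that clinicians use this as a sign that the block has worked, and that the numbness lasts long enough to put the lip and tongue at risk of injury.

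Under Sequence generation, the ICA arm is injected with the computerised device, whereas "A plastic syringe with a cartridge of 4% articaine 1:100,000 epinephrine will be used in the “IANB” group". The outcomes include a VAS of 0 with a completed pulpotomy as the definition of efficacy, and pain up to D+3. Follow-up is by telephone: "The patient will then be contacted by a research assistant 72h following the intervention by telephone to assess the pain perception". The same call asks about side effects.

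**The concern.** The person declared blinded is the one who feels the sign that separates the arms, and is also the one who scores the pain. If patients can work out their technique, expectation can enter every score given after the injection.

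The article suggests a direction. Its Discussion presents perforation with the ICA device as painless and the IANB as a fairly painful injection in acute pulpitis. It also anticipates that the new approach will increase the number of successful anaesthesias. A patient with similar expectations could report less pain with ICA. Efficacy requires a VAS of exactly 0, so any small non-zero report turns a success into a failure.

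A reader who accepts the single-blind label would assume that this source of bias had been controlled.

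**Working it through.** No arithmetic decides this point. It rests on setting the article's statements side by side and then asking which outcomes are exposed.

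**Step 1. What distinguishes the arms for the patient**

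| Feature | ICA | IANB | Where stated |
|---|---|---|---|
| Soft tissue numbness | None | Lower lip on the treated side, prolonged | Background; Discussion |
| Device | Computerised system that perforates bone | Plastic syringe | Sequence generation; Discussion |
| Injection site | Into the bone near the root apex | Near the mandibular foramen | Background |

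The first row matters most. Device and site are cues at the moment of injection, and masking at the chair might reduce them. Lip numbness is felt afterwards, and covering the patient's eyes or hiding the device would not remove it. Sequence generation gives every patient the same 1.8 mL, delivered by the technique of the assigned arm. Nothing in the article equalises the sensation between arms.

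**Step 2. Whether the stated reason supports blinding**

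The only reason offered is that the study is randomised. Randomisation determines how the arm is chosen. It does not determine whether the patient can recognise it afterwards. The conclusion does not follow, and step 1 points the other way.

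**Step 3. Which outcomes are exposed**

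| Outcome | Timing relative to injection | Source | Exposure |
|---|---|---|---|
| Corah anxiety score | Before | Patient | None |
| Pain at D0 | Before the operation | Patient | None |
| Baseline heart rate and blood pressure (T0 to T+4 min) | Before | Monitor | None |
| Time to return to baseline (primary) | After | Monitor | Lower |
| Pulpotomy completed (part of efficacy) | After | Not a patient score | Lower |
| VAS of 0 (part of efficacy) | Taken here as after; the article does not state the time | Patient | Direct |
| Pain at D+1 to D+3 | After | Patient | Direct |
| Side effects reported at the 72-h call | After | Patient | Direct |

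The comparison of pain change from D0 to D+3 is half protected, because D0 is collected before injection. The D+3 half is not.

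The primary outcome is not wholly immune. The Discussion names the patient's perception, fear and anxiety among the main causes of a raised heart rate. The readings still come from an instrument, and the remaining risk in applying the three-successive-values rule can be removed by hiding the arm code.

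**Step 4. What can still be changed**

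Trial status gives 1 July 2022 as the end of inclusion. The last 72-h call would then fall on 1 July + 3 days = 4 July 2022. The article was published on 5 December 2022. On that schedule, changes to the call would come too late. Changes to wording, to the derivation of the primary outcome and to interpretation would not depend on it.

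**The case against.** The strongest reply is that patients' knowledge of their arm is an inference. Each patient receives one technique and has nothing to compare it with. The information letter covers the trial's methods, but its text is not shown, so it may not say which technique numbs the lip. Some blocks may fail to numb it. This stands. A reader might infer that every patient will know the arm, or that correct guessing will run far above 50%. The article contains no figure for either, and the supportable wording is that patients can readily infer it. The IANB failure rates in the Background (44 to 81% in irreversible pulpitis) do not settle the matter: the Discussion says that lip numbness does not confirm pulpal anaesthesia, so those rates do not count patients without a numb lip.

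A second reply is that an article condenses its protocol. A sham procedure or a masked telephone interviewer may be described in the full document, so their absence here is not held against the plan. The point rests only on statements that are present and conflict.

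Third, because the disputed sentence stands under Allocation concealment mechanism, a reader might infer that concealment failed. The article does not support that. The Randomisation section describes a computer-generated list and centralised web allocation, released once the patient has been entered. Nor is patient blinding the only masking mentioned: Protocol violations provides for a blinded review of per-protocol assignment.

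Fourth, one might conclude that the trial should simply be called open-label. That goes too far, since not telling patients their arm before injection protects the anxiety score and the baseline readings.

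Finally, incomplete patient masking is largely inherent in comparing two injection techniques, and the affected outcomes are secondary. Both are true, and both argue for an accurate description rather than a change of design.

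**Conclusion.** The concern holds in limited form. The article asserts patient blinding, supports it with a reason that does not imply it, and elsewhere describes opposite soft tissue sensations in the two arms. This is an incorrect statement, not a missing detail. By the article's own account, blinding cannot be relied on after injection.

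The consequence falls on three patient-reported secondary measures: the VAS part of efficacy, pain at D+1 to D+3, and side effects. Measures taken before injection are unaffected and the monitor-read primary outcome is less exposed. The size of any bias in the pain scores cannot be derived from the article. Its likely direction, favouring ICA, assumes that patients share the expectations expressed in the Discussion.

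The conclusion assumes that the article's descriptions of numbness apply to most trial patients, and that the VAS in the efficacy definition is recorded after injection. It does not support a claim that all patients will know their arm, that allocation concealment failed, or that the primary comparison is invalid.

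**What to change.** - **Wording.** In the Abstract, Design, Interventions and Allocation concealment mechanism, replace the blinding claim with: *patients are not told their allocation before injection, but blinding is not expected to persist afterwards*. Delete the reasoning that randomisation blinds patients.
- **Primary outcome.** Apply the three-successive-values rule to the monitor readings with the arm code hidden.
- **Interpretation.** Report post-injection pain and side-effect comparisons as unblinded, and say so wherever efficacy is concluded.
- **Any patients still to be called.** Have the 72-h interview done by existing staff without access to the allocation. Add one question asking which technique the patient believes was used, and report it by arm. If inclusion ended as scheduled, this item lapses and the first three remain.

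Treatment, sample size and endpoints do not change. The cost is some editing, restricted access to the allocation for existing staff and, where still possible, one extra question. The downside is a less favourable design label and weaker efficacy conclusions.

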### Determination of sample size

The sample size calculation was based on the noninferiority hypothesis in a pilot study that there will be an expected mean difference of 1 min 30 s between the two anaesthetic techniques with regard to the time taken for the values to return to the initial ones. According to the reported results from the few studies available, the proportion of patients having successful anaesthesia and better pain control in the reference group (intraosseous anaesthesia) would be 93%. The noninferiority margin was defined as 20%. The significance was set at 1.7% for the 3 main criteria (heart rate, systolic and diastolic blood pressure) and 5% for the secondary criteria. Thus, using a bilateral test with an epiR package 0.98-87 (Biostatgv), 72 patients (36 patients per arm) will be included in the study.

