### Outcomes

The main outcome of this study is to compare the time required in minutes for the cardiovascular parameters to return to their initial values between the two techniques: ICA with the QuickSleeper™ system versus the reference technique: inferior alveolar nerve block (IANB). The timing of the evolution of the parameters is based on 3 phases: “baseline” from T0 to T+4 minutes, “anaesthesia” from T+4 to T+8 minutes, and “pulpotomy” from T+8 to T+14 minutes. The return to baseline values will be defined as a success if 3 successive values of heart rate and blood pressure (systolic and diastolic) are identical to those recorded before injection. On the other hand, if there is an absence of 3 successive values of these two parameters, it is defined as a failure.

Secondary outcomes include:The O^2^ measurement performed during the 3 phasesThe efficacy of the anaesthesia with a VAS (visual analogue scale) of 0 and that the pulpotomy was completed successfully: the patient is asked about his or her perception of pain before the operation at D0 and D+1, D+2, and D+3Post-operative careInvestigation of factors associated with delay in recovery of cardiovascular parameters (heart rate, dental anxiety, age, gender, and use of analgesics in the 6 h before surgery)

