### Statistical analysis

The analysis will be based on intention-to-treat (ITT) using the “missing=failure” strategy. A robustness analysis, supported by the per-protocol approach, will be carried out if the patients present with protocol deviations (error of randomisation). Qualitative variables will be described by the percentages and numbers of each modality. Quantitative variables will be described by means and standard deviations. Confidence intervals at 95% will be presented.

A paper case report form (CRF) will be created for each patient inclusion for data collection and will be based on the establishment of a clinical database. All information required by the protocol must be provided in the CRF, necessary for statistical analyses.

To assess the primary endpoint (time to return to baseline heart rate and blood pressure), the mean values will be estimated by the Kaplan-Meier method (survival curves) and compared using Log-Rank tests. To assess the secondary endpoint (time to baseline O_2_ and change in measurements over time), the 2 arms will be compared in the same way as the heart rate and blood pressure parameters. Univariate and multivariate Cox models will be used to investigate the factors associated with the time to the baseline of cardiopulmonary constants. The difference in pain between D0 and D+3 will be compared between the 2 groups a Student’s *t*-test or a Wilcoxon test. Data for the analysis are collected from the first questionnaire (French version of Corah’s dental anxiety scale), the three phases of cardiopulmonary monitoring, the VAS assessment, and the postoperative questionnaire given to the patient at the end of the procedure. The information recorded on the postoperative questionnaire will be collected by a telephone call 3 days after the procedure. All the data collected will be typed and inserted into an Excel spreadsheet for data entry in a secure computer network of Nantes University Hospital. The investigative team, mainly the investigators as well as the study technicians involved in this study protocol will have access to the data collected.

In regard to the post-trial care, the patients will either continue their dental care with their appointed dentist, or in the case where they do not have one, they will be following appointments at the Nantes University Hospital.

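### The sample size paragraph mixes two endpoints, so its 72 patients cannot be traced to the noninferiority primary question

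*Protocol article*

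**What the plan says.** Under Outcomes, the Protocol article sets the main outcome as being to "compare the time required in minutes for the cardiovascular parameters to return to their initial values between the two techniques". Successful anaesthesia (a VAS of 0 and a completed pulpotomy) is listed there among the secondary outcomes. Design describes the trial as a noninferiority study.

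Determination of sample size gives these inputs, in this order:

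- The basis: "The sample size calculation was based on the noninferiority hypothesis in a pilot study", namely that "there will be an expected mean difference of 1 min 30 s between the two anaesthetic techniques" in the time to return to initial values.
- A proportion: "the proportion of patients having successful anaesthesia and better pain control" is expected to reach 93% ("in the reference group (intraosseous anaesthesia) would be 93" per cent).
- A margin, directly after that proportion: "The noninferiority margin was defined as 20" per cent. Neither its scale nor its endpoint is named.
- Significance levels: 1.7% for the three main criteria (heart rate, systolic and diastolic pressure) and 5% for the secondary criteria.
- The result, from a two-sided test: 72 patients, 36 per arm.

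The paragraph states no SD, event rate, power or margin in minutes. For the primary endpoint, Statistical analysis says "the mean values will be estimated by the Kaplan-Meier method (survival curves) and compared using Log-Rank tests".

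**The concern.** The paragraph combines inputs that belong to different endpoints. The 1 min 30 s and the 1.7% level belong to the primary time-to-return outcome. The 93% belongs to a secondary outcome, which the same paragraph would test at 5%. The 20% follows the 93% and reads most naturally as a margin on that proportion. A noninferiority question about a time needs a margin in minutes or on another time-to-event scale such as a hazard ratio, and none is given.

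The role of 1 min 30 s is also unclear. It is called expected, inside a noninferiority hypothesis. If it is the anticipated true difference in the unfavourable direction, the margin must be larger, and no such margin appears. If it is the margin, the text does not say so.

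What is at stake is the conclusion the trial can draw. The Discussion hopes to find similar return times with the two techniques. The log-rank test examines equality and uses no margin, so failing to reject it does not show noninferiority. With no stated margin and no demonstrated power, a non-significant result on a safety-related endpoint could be reported as if it did.

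**Working it through.** **Inputs from the article:** proportion 93%, margin 20%, level 1.7% two-sided (0.85% in each tail), 36 per arm, difference 1.5 min. **Assumed here because not stated:** power (80% unless noted), the SD, the number of events, equal true success in both arms, and an absolute margin of 20 points. Normal quantiles: 2.387 for 0.85%, 0.842 for 80% power, 1.282 for 90%.

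**1. Can 72 be reproduced from the success proportion?**

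n per arm = 2 × 0.93 × 0.07 × (z_alpha + z_power)² / 0.20²

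- Two-sided 1.7%, 80% power: 0.1302 × (2.387 + 0.842)² / 0.04 = 33.9, so 34 per arm (68 in total).
- One-sided 2.5%, 90% power: 34.2, so 35 per arm (70).
- One-sided 5%, 95% power: 35.2, so 36 per arm (72).

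The match is exact only in the third case, whose settings the article does not state. At 36 per arm the standard error is √(0.1302/36) = 0.0601. Power at two-sided 1.7% is then Φ(0.20/0.0601 − 2.387) = 82.6%.

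**2. Can 72 be reproduced from the time difference?**

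Treating return time as a mean, the SD that makes 36 per arm sufficient is SD = 1.5 × √(36/2) / (z_alpha + z_power).

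- 80% power: 6.364 / 3.229 = 1.97 min.
- 90% power: 6.364 / 3.668 = 1.74 min (1.735 unrounded).

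This route can also give 36 per arm, but only with an SD that the article does not print. The two routes therefore do not identify which calculation was made.

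**3. What would 36 per arm deliver on the time scale?**

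Power = Φ(6.364/SD − 2.387). The same formula serves whether 1.5 min is a difference to detect or a margin with a true difference of zero.

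| Assumed SD (min) | Power at 36 per arm | n per arm for 80% power |
|---|---|---|
| 1.5 | 97% | 21 |
| 2.0 | 79% | 38 |
| 2.5 | 56% | 58 |
| 3.0 | 40% | 84 |

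For scale, the anaesthesia and pulpotomy phases run from T+4 to T+14. Times spread evenly over those 10 minutes would have an SD of 10/√12 = 2.9 min, so the tabulated range is plausible.

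**4. The planned log-rank test**

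Detectable hazard ratio = exp[(2.387 + 0.842) / √(events/4)], at two-sided 1.7% and 80% power.

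- 72 events: exp(3.229/4.243) = 2.14.
- 50 events: exp(3.229/3.536) = 2.49.

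Outcomes allows for patients who never show three successive matching values, so fewer than 72 events is realistic.

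**The case against.** The strongest objection is that this is a journal article condensing a full protocol that is not shown. The SD and the power may be in that document, and their absence alone would be no finding. That stands, and the point does not rest on it. It rests on what is printed: a secondary-outcome proportion and the margin that follows it, placed inside the justification for the primary endpoint.

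A reader might infer that 72 was in fact computed from the success proportion and that the 1 min 30 s played no part. The documents do not support that. The paragraph says the calculation rested on the time difference and uses the level of the cardiovascular criteria. The success inputs give 68 rather than 72 at that level with 80% power, and the time route reaches 72 with an SD near 2 min. The Fig. 1 caption, which describes a trial "evaluating the noninferiority of ICA QuickSleeper™ system versus IANB anaesthesia for the pain management", shows the same blurring of aims but is no evidence of how the number was derived.

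A reader might also infer that 72 is too few. That is not shown either, since an SD of at most about 1.97 min would give 80% power. The comparison-of-means figures are only a guide, because the planned analysis is a log-rank test. The extreme case, in which 1.5 min is both the true difference and the margin and power falls to 0.85%, needs a reading the article never states.

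Finally, inclusion was due to end on 1 July 2022, before publication in December 2022. Only the stated justification and the decision rule remain open to change.

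**Conclusion.** The concern holds as a defect in the printed basis of the sample size. The paragraph mixes two endpoints, its only margin follows a secondary-outcome proportion, and neither it nor the planned log-rank test supplies a margin for the primary endpoint. The 72 patients therefore cannot be traced to the noninferiority primary question.

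The size of the problem depends on an SD that is not given. Across assumed SDs of 1.5 to 3.0 min, power for 1.5 min at two-sided 1.7% runs from 97% down to 40%. The planned log-rank test could detect only hazard ratios of about 2.14 to 2.49 with 72 to 50 events. These figures assume normal approximations, 1:1 allocation and, for the hazard ratios, 80% power and proportional hazards. They do not establish where 72 came from or that it is inadequate.

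**What to change.** Rewrite Determination of sample size, and adjust Statistical analysis to match:

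1. State which calculation produced 72, with its power and all its inputs. Do not declare it sized for anaesthetic success unless that is what was done.
2. Remove the 93% and the 20% margin from the primary justification, or label them as belonging to the secondary efficacy outcome. Also reconcile the reference arm: this paragraph calls intraosseous anaesthesia the reference, while Outcomes gives that role to IANB.
3. State the primary noninferiority margin in minutes or as a hazard ratio, and say whether 1 min 30 s is that margin or the anticipated difference.
4. Report the power that 36 per arm gives for the primary analysis at 1.7%, using the pilot data.
5. Judge noninferiority by a confidence interval against that margin. For each of the three criteria, 1.7% two-sided corresponds to a 98.3% interval (100 − 1.7). State that a non-significant log-rank test does not by itself show noninferiority.

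The cost is one rewritten paragraph and a short addition to the analysis section. The rewrite itself adds no patients. The downside is that the stated power for the primary endpoint may be less favourable than readers now assume. If any outcome data have already been seen, the rewrite should say so, because a margin fixed afterwards carries less weight.
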